## Methods

### Study Design

The goal of this study is to evaluate whether the presence of respiratory symptoms, functional exercise incapacity, and COPD exacerbation rate across time are the same between the exposure group (users of iQOS with HeatSticks) and the control group (smokers of combustible cigarettes) through hypothesis testing.

In addition to this confirmatory goal, we would like to explore trends in spirometry results, chest CT scan results, prevalence of impaired quality of life, metabolic syndrome, abnormalities found by electrocardiography (ECG), physical exams, and serum lab tests among those who use iQOS with HeatSticks and those who currently smoke combustible cigarettes.

Exacerbation history will be collected prospectively (every 3 months) with the use of the adapted version of our proprietary SymptoMaster (Web, iOS, and Android) [16], and Medintel (Web) apps [17]. Symptoms history will be analyzed by clinical investigators. Should there be symptoms identified that are relevant to COPD, clinical investigators will approach health care organizations (serving participants in primary health care catchment area) to obtain ambulatory records of the use of antibiotics and/or systemic glucocorticoids or a health care utilization event.

Our primary confirmatory outcome variables are (1) presence of respiratory symptoms defined by CAT≥10, (2) functional exercise incapacity, and (3) exacerbation rate. The main exposure variable is smoking status (users of combustible cigarettes and users of iQOS with HeatSticks). The study groups are defined as:

Individuals (men and women) aged 40-59 years (inclusive) with a minimum of 10 pack-year smoking history who switched to and predominantly use the heated tobacco product iQOS with HeatSticks (exposure group). Predominant use of iQOS with HeatSticks is defined as >70% use.Individuals (men and women) aged 40-59 years (inclusive) who are currently smoking combustible cigarettes with a minimum of 10 pack-year smoking history (control group)

Pack-years will be calculated by taking the average number of cigarettes smoked per day divided by 20 and multiplied by the number of years smoked.

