### Inclusion and Exclusion Criteria

The study’s inclusion criteria comprise the following: male or female, aged 40-59 years, smoking history ≥10 pack-years (for all groups), and ability to follow study procedures. The exclusion criteria consist of the following:

pregnant womenlegally incapable individualspatients with history of chronic infectious and noninfectious lung disease except asthma (eg, pulmonary fibrosis, bronchiectasis, cystic fibrosis, tuberculosis) diagnosed prior to or during the first visit to the KAPM COPD Centerprevious surgical excision of at least one lung lobe (or having undergone a lung volume reduction procedure)active cancer of any localization under treatmentsuspected cancer of any localizationmetallic objects in the chestrecent eye surgery (within 6 months prior to the visit)episode(s) of myocardial infarction within 6 months prior to the visit or another form of acute or chronic coronary heart disease, history of heart rhythm abnormality with episode of arrhythmia within 6 months prior to the visit or long lasting that requires continuous drug therapyacute episode of cerebrovascular ischemic attack within 12 months prior to the visitchest or abdominal surgery performed within 6 months prior to the visitcontraindications to salbutamol or refusal to inhale salbutamolchest radiation therapy within 12 months prior to the visitradiology diagnostic procedures of chest within 6 months prior to the visitrecent (6 weeks before visit) respiratory tract infection (colds, flus), fever of any etiology with increasing temperature >37^°^C at the time of the visit and 2 weeks prior to the visitsignificant history of alcohol abuse or consumption of more than recommended units of alcohol per week (28 units male and 21 units female)positive screening test for HIV antibodies or positive screening for TB, if available at the time of first visitelevated blood pressure (systolic) ≥160 mmHg at the time of visitemployees of Philip Morris International and first-degree relatives who are employees of Philip Morris International

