As a result, the sample size of 1041 respondents is enough to detect significant differences in three primary confirmatory outcomes with at least 80% power. However, in addition to dropouts, we need to consider that participants may switch from one tobacco product to another, quit smoking, use several tobacco products at the same time, and the fact that a nonrandomized observational study needs to be adjusted for confounding factors. Even if most of these events do not cause subjects’ withdrawal, they lead to a decreased number of participants for further statistical analysis. Therefore, we need more participants to solve this issue. We propose recruiting 400 participants in the exposure (iQOS) cohort and 800 participants in the control (combustible cigarettes) cohort. The following sample size should allow us to achieve the confirmatory goal of the study: (1) iQOS with HeatSticks smokers (exposure group, N=400) and (2) conventional cigarette smokers (control group, N=800; total sample size=1200).

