We will apply a three‐stage reporting framework [27]. Model 1 will report the crude analysis (without any adjustments for confounders), Model 2 will report the semi‐adjusted analysis (including the following a priori defined covariates of gender, age, number of pack-year at base-line), and Model 3 will present the fully adjusted model (including all the covariates as in Model 2 plus those covariates that have discrepancies across two cohorts and change the estimate of association). The matching variables can be ignored in the model if we have exactly two controls for each participant in the iQOS cohort. Because of dropouts and other reasons, that will be impossible to achieve. There will be some confounder effect remaining, which means we have to include matching variables in the analysis. Model diagnostic plots will be generated to test model assumptions, for example, normality of deviance residuals.

We will also use two methods of propensity score analysis (PSA)—stratification on the propensity score and inverse probability weighting using the propensity score [28]—to adjust for confounders that may vary in study groups.

For missing data analysis, we will use missing at random assumptions. Missing values will be handled by multiple multivariate imputation in R. We will analyze five copies of the data, each with missing values imputed, in the GEE/GLMM multivariate analysis. The estimates of association will then be averaged according to Rubin’s rule [29] to produce a single mean estimate and adjusted standard errors.

To address dual usage, switching, and quitting, we will use several methods. First, we will implement the intention-to-treatment strategy, that is, we will adjust only for baseline confounders and evaluate the exposure effect as if all study participants remain under the exposures at the baseline until end of follow‐up. Second, we will evaluate the exposure effect censoring switchers and quitters from the analysis. Third, particularly for dual usage, we will model two exposures, iQOS and conventional cigarette usage, as weighted sums of doses calculated in pack-years. Weights will depend on the importance of the different periods, where the closest period will have the highest weight.

Analysis will be done using R [19]. The Bonferroni correction of the significance level will be applied to account for three confirmatory hypotheses being tested in the study, so an alpha <.017 (0.05/3) will be considered significant.

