Sensitivity analysis will be performed to assess consistency of the effect estimate by testing variations in underlying assumptions. First, we will assess potential biases due to unmeasured confounders or how strong should be an unmeasured confounder to explain the magnitude of the effect estimate. Second, we will consider the use of more than one cohort definition to ensure that the effect estimate is robust to the assumptions behind these definitions. For example, we will use a different cut-off for predominant use of iQOS with HeatSticks (>50%, >60%, >70%, >80%, >90%, 100%) based on averaging iQOS percentage use over time beginning from baseline. Third, there are several alternative statistical analysis approaches to evaluate the effect estimate. We will explore whether the choice of statistical method (GEE/GLMM/PSA) will influence the effect estimate. Finally, we will search how redefining the threshold (ie, different cut-off points for binary outcomes, CAT, and 6MWT) changes the effect estimate.

All study data will be stored at the Information Technology Unit of КАPM. Data will be entered through a Web-accessible system. The questionnaire will be designed as an HTML Web form and will be placed on the server so that it can be loaded and displayed through the client browser at the time of connection. Data analysis will be done only in aggregate. All data will be used for research purposes only, and no participant will be identified when the data are analyzed, presented, or published. No individually identifiable information will be published. The Ethics Committee of KAPM approved this study on December 5, 2017.

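### Controls have no upper limit on iQOS use, which dilutes the baseline-group comparison, and the cut-off sensitivity analyses assign cohorts by product use after baseline

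*Protocol article*

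**What the plan says.** Study Design in the protocol article defines the two cohorts. The exposed cohort has a share rule: "Predominant use of iQOS with HeatSticks is defined as >70% use". The control cohort consists of people "who are currently smoking combustible cigarettes with a minimum of 10 pack-year smoking history (control group"), with no statement about iQOS or other alternative products. The inclusion list under Inclusion and Exclusion Criteria reads "male or female, aged 40-59 years, smoking history ≥10 pack-years (for all groups), and ability to follow study procedures", and none of the exclusions concerns product use.

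The article expects mixed use. Sample Size Calculation notes that "participants may switch from one tobacco product to another, quit smoking, use several tobacco products at the same time", and gives this, together with confounding, as the reason for going from 1041 to 1200. Table 1 itself adjusts for dropout only.

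The Statistical Analysis and Data Management Plan lists three strategies for dual use, switching and quitting. In the first, "we will adjust only for baseline confounders and evaluate the exposure effect as if all study participants remain under the exposures at the baseline". The second reads "Second, we will evaluate the exposure effect censoring switchers and quitters from the analysis". The third models recency-weighted doses of both products. Among the sensitivity analyses, iQOS cut-offs from >50% to 100% are applied, "based on averaging iQOS percentage use over time beginning from baseline".

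**The concern.** One side of the comparison has a numerical product-share rule and the other has none. The text guarantees only that exposed participants are above 70% iQOS. It does not guarantee that controls are at or near zero. The effects used for the sample size (odds ratios 0.27 and 0.62, rate ratio 0.5) assume that iQOS users differ from smokers as ex-smokers do, which is a full contrast. Dual users among the controls reduce the contrast actually studied, and analysis by baseline group inherits that loss.

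The averaged-use cut-offs raise a different problem. When cohort membership depends on use averaged over follow-up, use in later years helps decide the group in which a year-1 outcome is counted. CAT symptoms are a confirmatory outcome and are also a plausible reason to change product, so the outcome can influence the exposure label. An analysis offered as a robustness check could then move for reasons unrelated to the product.

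The censoring strategy has a related but softer weakness: leaving the analysis by quitting or switching may depend on symptoms.

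**Working it through.** **Inputs from the article.** Two-sided alpha 0.017, power 80%, ratio 1:2. Table 1 after dropout: 31/62 (CAT), 347/694 (walk test), 340/680 (exacerbations). Planned recruitment 400/800.

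**The plan's own figure.** Dividing the pre-dropout exposed numbers by 0.75 gives 23 → 31, 260 → 347 and 255 → 340, all as tabled, and 347 + 694 = 1041. The pre-dropout numbers come from simulations whose random-effect variance and visit set are not given. A group-by-time calculation with independent observations, visits 0–5 and no group main effect gives 80.6% for CAT and 78.0% for the walk test. For exacerbations it gives 85.9% (78.7% with visits 0–4). That is near the stated 80%, but only under these added assumptions. Below, Table 1 is taken at its word.

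**Power at 400/800 when contrast is lost.** Let s be the fraction of the assumed log effect that remains. With z(0.0085) = 2.387 and z(0.20) = 0.842, the sum is 3.228, and

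power = Φ(3.228 × s × √(400/n) − 2.387), with n = 347 (walk test) or 340 (exacerbations).

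| s | Walk test | Exacerbations |
|---|---|---|
| 1.0 | 86% | 87% |
| 0.9 | 77% | 78% |
| 0.8 | 65% | 66% |
| 0.7 | 52% | 53% |

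For the walk test at s = 0.9: 3.228 × 0.9 × 1.074 − 2.387 = 0.73, and Φ(0.73) = 0.77. CAT, with n = 31, stays above 98% down to s = 0.4.

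One way to reach s = 0.9 is for 20% of controls to be dual users who get half the benefit: 1 − 0.20 × 0.5 = 0.90, if benefit is linear on the log scale. All these inputs are assumptions, because the article gives no dual-use prevalence.

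**What the extra recruits absorb.** Power stays at 80% while s ≥ √(347/400) = 0.931 (walk test) or √(340/400) = 0.922 (exacerbations), a loss of about 7–8%.

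**Averaged use, by hypothetical case.** Tables 2 and 3 schedule smoking status at baseline and at four annual visits.
- An iQOS user at 100% on the first two assessments who develops symptoms and returns fully to cigarettes averages (100 + 100 + 0 + 0 + 0)/5 = 40%. That person fails every cut-off, and the early symptomatic record leaves the iQOS cohort. This favours iQOS.
- If the rule is applied to everyone, a symptomatic smoker at 0% at baseline who then switches fully averages 400/5 = 80%. That person passes >70% and brings the symptomatic baseline into the iQOS cohort.

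The two cases put early symptoms on opposite sides of the comparison, so the net direction is not fixed.

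**Censoring.** In those remaining at one visit, observed OR = true OR × (rE / rC). Here r is the retention of symptomatic people divided by the retention of asymptomatic people, in the exposed (E) and control (C) cohorts. The Table 1 prevalences, 17% and 42.8%, give a true OR of 0.274. Suppose 40% of symptomatic and 20% of asymptomatic people are censored, so r = 0.6/0.8 = 0.75 (assumption).
- Both cohorts: prevalences become 13.3% and 35.9%, and the OR stays at 0.274.
- Controls only: 0.274/0.75 = 0.365.
- iQOS cohort only: 0.274 × 0.75 = 0.21.

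Bias in the OR therefore needs symptom-related censoring that differs between cohorts.

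**The case against.** The strongest reply is that the article condenses a fuller protocol. Table 2 has smoking status and iQOS use reviewed for eligibility at screening, so a working rule for controls may exist. That is possible. But the article states both definitions, puts a number on one and leaves the other open, so anyone following it would admit the 60% user.

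A reader might infer that someone with 75% iQOS and 25% cigarettes can be placed in either cohort. Taken literally the wording allows it, but the definitions are set out as alternatives and the specific rule points that person to the exposed cohort. The firm gap is the current smoker at or below 70% iQOS.

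A reader might also infer that 80% power becomes 70%. That starts from 1041 participants and ignores the increase to 1200, which was made partly for multiple product use. Nor does the text support a shift in the odds ratio from 0.27 to about 0.36 through censoring. That needs censoring in controls alone, whereas cessation advice goes to both cohorts and quitting is expected in both.

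It would be too strong to say that the supplementary analyses cannot confirm the main result. The first-listed strategy uses baseline groups and has no post-baseline selection. The dose model covers dual use in part, and a >50% cut-off would class a 60% user as iQOS. A likelihood mixed model that keeps visits before censoring can handle censoring that depends on earlier observed scores, and censoring weights are commonly left to the analysis plan, which is not shown. The missing ceiling and the averaged-use rule remain, because both rest on stated text.

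**Conclusion.** The point holds in two parts, with a third as a recommendation.

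First, the control definition admits dual users and so dilutes the baseline-group comparison. The pull is toward no difference, so it cannot by itself produce a false harm-reduction finding. The cost is power. For a 10% loss of log effect, power falls to about 77% (walk test) and 78% (exacerbations), just under target, with CAT hardly touched. These figures rest on Table 1 being right, on a linear dose assumption and on an assumed amount of dual use. The true loss cannot be computed from the article.

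Second, cut-offs based on use averaged over follow-up let later behaviour label earlier outcomes. That symptoms drive product change is plausible but is an inference, and neither the direction nor the size of the bias is known.

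Third, the analysis that censors switchers and quitters would benefit from weighting. Its bias in the odds ratio depends on censoring that differs by symptoms between cohorts, which the article neither shows nor rules out.

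**What to change.** - **Control definition.** State a ceiling on baseline iQOS use for controls that does not overlap the exposed definition, and apply it with the product-use data collected at screening and baseline.
- **Participants already enrolled.** Report the baseline-group analysis with and without controls above the ceiling, keeping the matching variables in the model.
- **Cut-off analyses.** Define the cohorts by baseline use, or by use up to the previous visit as a time-updated exposure.
- **Censoring analysis.** Add inverse-probability-of-censoring weights built from earlier CAT, walk-test, exacerbation and product-use data, or label the analysis exploratory.

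Everything needed is already scheduled: product use and the iQOS switch date in the interview questionnaire, and smoking status, CAT and the walk test at the annual visits. The cost is one sentence of definition and some programming. Weighted intervals will be somewhat wider. Removing controls above the ceiling loses some of them and breaks some 1:2 sets. The number affected is unknown; under the 20% illustration it would be up to 0.20 × 800 = 160, depending on where the ceiling is set.

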### Inclusion and Exclusion Criteria

The study’s inclusion criteria comprise the following: male or female, aged 40-59 years, smoking history ≥10 pack-years (for all groups), and ability to follow study procedures. The exclusion criteria consist of the following:

pregnant womenlegally incapable individualspatients with history of chronic infectious and noninfectious lung disease except asthma (eg, pulmonary fibrosis, bronchiectasis, cystic fibrosis, tuberculosis) diagnosed prior to or during the first visit to the KAPM COPD Centerprevious surgical excision of at least one lung lobe (or having undergone a lung volume reduction procedure)active cancer of any localization under treatmentsuspected cancer of any localizationmetallic objects in the chestrecent eye surgery (within 6 months prior to the visit)episode(s) of myocardial infarction within 6 months prior to the visit or another form of acute or chronic coronary heart disease, history of heart rhythm abnormality with episode of arrhythmia within 6 months prior to the visit or long lasting that requires continuous drug therapyacute episode of cerebrovascular ischemic attack within 12 months prior to the visitchest or abdominal surgery performed within 6 months prior to the visitcontraindications to salbutamol or refusal to inhale salbutamolchest radiation therapy within 12 months prior to the visitradiology diagnostic procedures of chest within 6 months prior to the visitrecent (6 weeks before visit) respiratory tract infection (colds, flus), fever of any etiology with increasing temperature >37^°^C at the time of the visit and 2 weeks prior to the visitsignificant history of alcohol abuse or consumption of more than recommended units of alcohol per week (28 units male and 21 units female)positive screening test for HIV antibodies or positive screening for TB, if available at the time of first visitelevated blood pressure (systolic) ≥160 mmHg at the time of visitemployees of Philip Morris International and first-degree relatives who are employees of Philip Morris International

### Sample Size Calculation

Based on the results of the cross-sectional study, we demonstrated that smoking cessation alleviates activity limitations and airway disease caused by smoking of combustible cigarettes. This is evidenced by the prevalence of a CAT score of ≥10 among those who stopped smoking during the past 1-5 years at 17% compared to 42.8% among current smokers, and reduced inability to walk 450 meters within 6 minutes on 6MWT (11% compared to 16.7% among current smokers).

We hypothesize that switching from combustible cigarettes to iQOS with HeatSticks may reduce the risk of respiratory exacerbation and other COPD manifestations, somewhat similar to the effects of smoking cessation observed in the cross-sectional study.

In the cross-sectional study, duration of smoking abstinence in the second (ex-smoker) study group varied from 1-5 years. This is comparable with the length of the cohort study (5 years) that we propose. Therefore, we can use estimates of the outcome variables derived from the cross-sectional study to calculate required sample sizes that can identify statistically significant differences.

We suggest implementing a matched-pair cohort study design where a pair contains one iQOS with HeatSticks user and two conventional cigarette users matched by gender, age, education, and baseline exposure level (number of pack-year). By selecting this study design, we take into account the limited number of iQOS users from which the first (exposure) cohort is planned to be recruited.

To perform sample size calculation, we will assume that the associations we observed in the cross-sectional study between primary confirmatory outcomes and the smoking status (ex-smokers vs current combustible cigarette smokers) will be the same for iQOS users as compared to combustible cigarette smokers at the final visit after 5 years:

At the final visit, the odds ratio of association between the exposure and CAT score of ≥10 will equal 0.27 and a CAT ≥10 prevalence will be 42.8% in the control group.At the final visit, odds ratio of association between the exposure and inability to walk 450 meters on the 6MWT will equal 0.62 and a 6MWT <450 meters prevalence will be 16.7% in the control group.At the final visit, rate ratio of association between the exposure and exacerbations will equal 0.5 and annual exacerbation rate will be 0.1 in the control group based on conservative estimations from Woodruff et al [10]. We also assume that these associations will increase steadily from 1 to the above-indicated values. Sample size calculations for three primary confirmatory outcomes have been performed by simulations and the frequentist method based on the power and level of significance of a test. For each primary confirmatory outcome, we have generated data from the distribution assumed for the combustible cigarette smokers and the distribution for the iQOS with HeatSticks smokers (based on our assumptions of how their changes in respiratory symptoms prevalence, proportions of participants who walk less than 450 meters, and annual exacerbation rate might be different if switched from combustible cigarettes to iQOS with HeatSticks). We have used R [19] for simulations (1000 simulations per each primary confirmatory outcome variable) and fitting a generalized linear mixed-effects model (GLMM) on simulated data (function “glmer” in the package “lme4”). For sample size calculation, we have used a power value of 80%, two-sided significance level (alpha) 1.7% that accounts for multiple hypotheses testing, and 1:2 ratio for sample sizes of the experimental and control cohorts.

Then, we have adjusted the sample size for anticipated proportion of dropouts (taking into consideration a 10% annual dropout rate and the fact that already collected data relating to any participant who stops the study early will be analyzed). Sample size calculations are presented in Table 1.

As a result, the sample size of 1041 respondents is enough to detect significant differences in three primary confirmatory outcomes with at least 80% power. However, in addition to dropouts, we need to consider that participants may switch from one tobacco product to another, quit smoking, use several tobacco products at the same time, and the fact that a nonrandomized observational study needs to be adjusted for confounding factors. Even if most of these events do not cause subjects’ withdrawal, they lead to a decreased number of participants for further statistical analysis. Therefore, we need more participants to solve this issue. We propose recruiting 400 participants in the exposure (iQOS) cohort and 800 participants in the control (combustible cigarettes) cohort. The following sample size should allow us to achieve the confirmatory goal of the study: (1) iQOS with HeatSticks smokers (exposure group, N=400) and (2) conventional cigarette smokers (control group, N=800; total sample size=1200).

